## Abstract

**Background:**

Antipsychotic-induced Weight Gain (AiWG) is a debilitating and common adverse effect of antipsychotics. AiWG negatively impacts life expectancy, quality of life, treatment adherence, likelihood of developing type-2 diabetes and readmission. Treatment of AiWG is currently challenging, and there is no consensus on the optimal management strategy. In this study, we aim to evaluate the use of metformin for the treatment of AiWG by comparing metformin with placebo in those receiving treatment as usual, which includes a lifestyle intervention.

**Methods:**

In this randomized, double-blind, multicenter, placebo-controlled, pragmatic trial with a follow-up of 52 weeks, we aim to include 256 overweight participants (Body Mass Index (BMI) > 25 kg/m^2^) of at least 16 years of age. Patients are eligible if they have been diagnosed with schizophrenia spectrum disorder and if they have been using an antipsychotic for at least three months. Participants will be randomized with a 1:1 allocation to placebo or metformin, and will be treated for a total of 26 weeks. Metformin will be started at 500 mg b.i.d. and escalated to 1000 mg b.i.d. 2 weeks thereafter (up to a maximum of 2000 mg daily). In addition, all participants will undergo a lifestyle intervention as part of the usual treatment consisting of a combination of an exercise program and dietary consultations. The primary outcome measure is difference in body weight as a continuous trait between the two arms from treatment inception until 26 weeks of treatment, compared to baseline. Secondary outcome measures include: 1) Any element of metabolic syndrome (MetS); 2) Response, defined as ≥5% body weight loss at 26 weeks relative to treatment inception; 3) Quality of life; 4) General mental and physical health; and 5) Cost-effectiveness. Finally, we aim to assess whether genetic liability to BMI and MetS may help estimate the amount of weight reduction following initiation of metformin treatment.

**Discussion:**

The pragmatic design of the current trial allows for a comparison of the efficacy and safety of metformin in combination with a lifestyle intervention in the treatment of AiWG, facilitating the development of guidelines on the interventions for this major health problem.

**Trial registration:**

This trial was registered in the Netherlands Trial Register (NTR) at https://www.trialregister.nl/trial/8440 as NTR NL8840 on March 8, 2020.

## Background

Antipsychotics are the mainstay treatment modality for schizophrenia. Antipsychotic-induced Weight Gain (AiWG) is a debilitating and prevalent adverse effect. Antipsychotics are associated with weight gain, lipid and glucose dysregulation and therefore increase the risk for the development of metabolic syndrome (MetS) [1–5]. After the initation of antipsychotic treatment in medication-naïve patients, the average increase in Body Mass Index (BMI) is 1.8 units in 12 weeks and 3.9 units in 48 weeks [6]. The relative risk for obesity is up to two in schizophrenia patients using antipsychotics compared to the general population [7]. The increased obesity rate in schizophrenia patients can be mainly attributed to the use of antipsychotics [8]. Obesity is a major health problem resulting in increased morbidity and mortality, thus decreasing life expectancy and increasing pressure on healthcare budgets [9, 10]. Schizophrenia patients have a reduced life expectancy of 20% compared to the general population and approximately one third of patients with schizophrenia have MetS [5, 11]. Moreover, the relative risk of MetS for people with severe mental illness is 1.58 compared to the general population [11]. Importantly, all antipsychotics are to variable degrees associated with AiWG. For example, in a retrospective study of many antipsychotics, AiWG was highest for olanzapine with 4.2 kg and lowest for amisulpride at 1.8kgs measured over a period of 3 years [12]. Aripiprazole and haloperidol have been reported to result in relatively mild or in some studies no AiWG. AiWG also negatively impacts quality of life, treatment adherence, likelihood of developing type-2 diabetes and readmission rate [13–15]. Considering the growing mortality gap between schizophrenia patients and the general population, additional management strategies to increase the life expectancy of schizophrenia patients are necessary [16].

Despite these broad clinical implications of AiWG, treatment of AiWG has not yet been optimized. Most guidelines, including the Dutch national guideline for schizophrenia, recommend the following interventions for AiWG: 1) switching of antipsychotic; or 2) weight reduction through lifestyle interventions (diet and exercise) [17]. The impact of switching antipsychotic treatment is limited as the vast majority of antipsychotics is associated with weight gain [18]. Weight reduction through lifestyle interventions is viable but known for its relatively variable efficacy. For example, a recent study found a statistically significant effect of lifestyle interventions on weight in people with severe mental illness that was considered clinically insignificant, while a meta-review of meta-analyses found individual lifestyle counselling and exercise alone (i.e. planned, structured intensive physical activity) as the most effective weight reduction intervention in patients with schizophrenia [19, 20]. Of note, integrated interventions combining multiple lifestyle components (e.g. exercise and diet) delivered by qualified professionals (e.g. dietitian, exercise professionals) may be most effective for health-related outcomes and adherence, although such interventions have been less studied yet [21–23]. In this context, many guidelines, including the 2018 WHO guidelines and the Dutch national guideline for schizophrenia, recommend lifestyle interventions as first-line strategy for the management of physical health in people with severe mental illness, including AiWG [17, 24]. However, given the extensive challenge to clinically significantly reduce AiWG and the only partial contribution of lifestyle interventions to help lose weight, there is a clear need for additional (combined) strategies to manage AiWG.

Metformin is a promising agent in the treatment of AiWG. Metformin generally promotes satiety and increases Glucagon-like Peptide (GLP-1), thus often resulting in reduced energy intake [25]. Clozapine reduces the production of GLP-1 and therefore is a viable treatment option for clozapine-induced weight gain [25]. Meta-analyses conclude that of all agents studied as monotherapy for AiWG, metformin is most effective in attaining weight loss for child and adolescent schizophrenia patients and for those patients who use clozapine [26, 27].

Recently, a meta-analysis investigated the combination of metformin and lifestyle interventions as a treatment for AiWG, reporting only one double-blinded trial on this topic [28, 29]. Additionally, five open label studies were included, published in Chinese journals which are not indexed by Pubmed and found to be of poor quality [29–34]. That double-blinded, well powered randomized controlled trial of sufficient quality comparing lifestyle interventions with and without concomitant use of metformin in Chinese antipsychotic users found metformin, lifestyle interventions and the combination of metformin and lifestyle interventions to be superior to placebo [28]. The best results on body weight, waist circumference and BMI were obtained for the combination of lifestyle plus metformin. Important limitations of that trial and any previous trials of AiWG done with metformin are the strict inclusion criteria with regards to diagnosis (no other diagnoses than first-episode schizophrenia allowed in that previous trial) and the amount of AiWG, thus not adequately reflecting schizophrenia patients encountered in general practice [28]. Furthermore, a very extensive exercise program (seven times a week) was implemented in this trial and we question the applicability of such an intensive intervention. Moreover, the duration of treatment was short (12 weeks) and the doses of metformin were relatively low (mostly around 1000 mg daily), even though efficacy may be better with higher doses without a negative impact on tolerance [35, 36]. Finally, all aforementioned trials were conducted before the COVID-19 pandemic, which has heavily impacted both research and clinical activities across the globe. Particularly lifestyle sessions with many individuals, often placed in the same indoor space, are challenging to conduct in the current era with social distancing and lockdowns in place in several countries and the possible scenario of a future virus affecting global health.

## Objectives

In sum, the treatment of AiWG is currently very challenging and few interventions have been investigated in well powered trials of sufficient quality. Therefore, this randomized, double blind, multicenter, placebo-controlled, pragmatic trial aims to evaluate the effect of metformin doses up to 2000 mg daily for AiWG as an additional strategy next to treatment as usual including lifestyle interventions, by comparing metformine plus the lifestyle intervention with placebo plus the lifestyle intervention. In the event of a significantly greater reduction of AiWG following metformin use in combination with care as usual including a lifestyle intervention, guidelines can include metformin for AiWG. Furthermore, we aim to investigate the difference in metformin-associated reduction of AiWG between participants using clozapine versus other antipsychotics; between participants on high-AiWG risk agents (i.e. olanzapine, clozapine, quetiapine, risperidone and paliperidone) compared to all other antipsychotics; and the difference between self-reported weight gain due to antipsychotic use versus weight gain due to other reasons [2, 12]. At last, we aim to examine whether lifestyle interventions in combination with metformin or placebo improve metabolic traits, quality of life, general physical and psychological health, cost effectiveness, and whether genetic liability to BMI and MetS allows adequate estimation of weight reduction following initiation of metformin and lifestyle interventions.

Metformin and placebo both combined with treatment as usual including lifestyle interventions are the conditions we wish to evaluate with difference in body weight as the primary outcome measure. We hypothesize that metformin given adjunctively to lifestyle interventions will lead to a higher level of weight reduction and better quality of life, compared to placebo in combination with lifestyle interventions.

## Methods

### Study setting

This multi-center trial will be conducted at the University Medical Centre Utrecht (UMCU), Mondriaan Mental Health Maastricht and GGNet Mental Health in the Netherlands. The estimated duration of this study is 3.5 years (including a participants’ enrolment phase) and participants will be followed-up for 52 weeks. The study has been approved by the Medical Research Ethics Committee Utrecht and was registered at the Netherlands Trial Register (NL8840). The study will be conducted according to the principles of the Declaration of Helsinki (amended version in October 2013) and following Good Clinical Practice guidelines from the European Medicines Agency (ICH E6, R2) and the Medical Research Involving Human Subjects Act (WMO).

### Study population

One hundred tewnty-eight participants with a schizophrenia spectrum disorder will be followed-up for 26 weeks. With an estimated attrition rate of 50% based on attrition rates of previous trials targeting schizophrenia patients, a total of 256 participants will be recruited from the participating and referring centres in the Netherlands (see ‘sample size calculation’ below) [37]. Two groups of subjects with psychotic disorders will be recruited: 1) general patients suffering from psychosis who use a range of antipsychotics; and 2) those considered (relatively) treatment-resistant who are treated with clozapine. We specifically chose both patients on clozapine and patients on other antipsychotics given possible differences in the efficacy of metformin for both patient groups: metformin may be a particularly viable treatment modality for clozapine-induced weight gain as clozapine-induced decreases in GLP-1 may be partially offset by metformin’s GLP-1 increasing effects [25]. Eligibility of all possible participants will be determined following intake questions, physical examination and laboratory findings. Should any of the results from the intake visit require immediate attention, the treating physician will contact the participant’s general practitioner (GP).

### Recruitment

Participating and referring sites will be recruiting. At participating sites, participants will be recruited by treating psychiatrists, psychologists and general practitioners. The participants will be informed and asked for written informed consent by a research-physician or P.I. Referring sites provide contact details of possible eligible participants to participating sites after the patient has provided consent. In addition, referring sites will ask participants for their consent that a participating site can approach the participant. Referring sites have no part in the inclusion process. Referring and participating sites can use posters and brochures to recruit eligible participants. Furthermore, physician brochures will be used to inform treating physicians and to support the process of recruitment. Enrolment of participants, obtaining informed consent and randomization will be performed by authorized personnel of the research team of participating sites.

### Inclusion criteria

Diagnosis of schizophrenia spectrum disorders according to DSM-IV-TR or DSM-5 criteria as summarized in DSM-IV or DSM-5 chapter Schizophrenia Spectrum and other Psychotic Disorders, except for substance/medication-induced psychotic disorder, psychotic disorder due to another medical condition, catatonia associated with another mental disorder, catatonic disorder due to another medical condition, and unspecified catatonia;Antipsychotic use for at least 3 months (as most AiWG occurs in the first weeks to months of treatment);Willingness to participate in a lifestyle intervention;Dutch speaking and reading;Mentally competent according to the treating physician;Able to give informed consent;At least 16 years of age;Overweight (BMI > 25).

### Exclusion criteria

Neurodegenerative extrapyramidal disease;Metformin-related contraindications: i.e., conditions predisposing to tissue hypoxia (such as congestive heart failure, recent myocardial infarction and respiratory failure), metabolic acidosis, precoma diabeticum, kidney failure (glomerular filtration rate (GFR) < 30 ml/min) and conditions predisposing to kidney failure (e.g. dehydration, infections and hypovolemic shock), disorders in the use of alcohol defined as > two reported consumptions daily and/or a gamma-glutamyltransferase (GGT) of over 60 U/L, and liver failure;Current use of medication(s) that inhibit(s) metabolism of metformin or otherwise interacts with metformin (in particular those with possible detrimental effects on kidney functioning):-Non-steroidal anti-inflammatory drugs (NSAIDs).-Angiotensin converting enzyme-inhibitors (ACE-inhibitors).-Angiotensin receptor blockers (ARBs).-Diuretics.-Organic cation transporters (OCT) -1 and 2 inhibitors (e.g. cimetidine, dolutegravir, isavuconazol, trimethoprim, vandetanib, crizotinibib, vandetanib, and verapamil) and inductors (e.g. rifampicin);Vitamin B12 deficiency defined as a Vitamin B12 serum level of < 148 pmol/L [38];Diabetes mellitus according to NHG-criteria [39];Pregnant or breast feeding women or women of child bearing age using no contraceptives.

### Randomization and blinding

After eligibility screening and providing written informed consent, participants will be randomized using block-randomization with a 1:1 allocation to 1) placebo; or 2) metformin. Randomization will be stratified for clozapine use versus other antipsychotic use additional to stratification for participating sites using a computer-generated double-blind application developed by the UMC Utrecht’s Data Management department. The block sizes will not be disclosed. Allocation concealment will be facilitated by releasing the randomization code only after the participant has completed all baseline assessments and has been included in the trial.

The participant, caregiver, investigator and outcome assessor will be blind to treatment allocation. Placebo tablets will be matched to metformin tablets in size and appearance. Unblinding for all participating sites will be performed by the study sponsor whenever needed for safety reasons. For this purpose, a set of sealed envelopes comprising the information on the type of medication stored in every medication box used in the trial will be sent to the UMC Utrecht pharmacy. This pharmacy will provide a 24/7 backup emergency unblinding service. Participants will be excluded from subsequent statistical analyses after unblinding of the treatment allocation.

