### Statistical analysis

#### Sample size calculation

A regression of weight on treatment with a sample size of 128 observations achieves 80% power at a two-sided 0.05 significance level to detect a difference in a weight reduction of two kgs (SD = 4, ES = 0.5) after 26 weeks (PASS 2008, version 8.0.16). We estimate the drop-out rate to be a maximum of 50% as such attrition rates are most commonly reported in trials targeting schizophrenia patients [37]. Drop-outs are those not attending the visit at 26 weeks. As soon as 128 subjects have completed this visit, inclusion will be stopped. Considering the estimated drop-out rate, we will therefore include approximately 256 subjects to ensure that 128 subjects complete the visit at 26 weeks. This power calculation is based on an independent two-sample t-tests of the outcome at 26 weeks. Using linear models in the data analysis will increase the efficiency of the analysis and therefore the power to detect a treatment effect.

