#### Data analysis

The primary analysis in this trial tests the effect of metformin use next to care as usual including lifestyle interventions on body weight with a primary comparison at 26 weeks after treatment onset. This will be analyzed using a general linear mixed model with treatment group, baseline weight, gender, age, timepoint (as categorical factor) and compliance with lifestyle therapy as fixed factors and patient as random factors. Measurements of visit 3 (week 13) and visit 4 (week 26) will be included in the primary analysis models. Missing baseline parameters will be imputed before the analyses, but mixed models can handle missing outcome variables at post-randomization weeks if these are missing at random (MAR). The pattern of missingness will be examined. As a sensitivity analysis, body weight at 26 weeks will also be analyzed using an ANCOVA with treatment group and gender as factors and baseline weight and age as covariates. The significance threshold is set at *p* < 0.05. Considering the study population, we expect a high number of dropouts [37]. Additionally, we expect participants within one stratification group may switch clozapine or other antipsychotic use. Taking into account the pragmatic design of this study, the Intention-To-Treat principle will be followed for the primary and secondary analyses. In secondary analysis, the effect of metformin on body weight after 26 weeks of treatment will be compared to body weight at 52 weeks after 26 weeks of non-treatment with metformin. In this way, we can examine whether the possible effect of metformin on AiWG continues after 26 weeks of non-treatment following discontinuation of metformin use after 26 weeks of treatment. In a sensitivity analysis, per-protocol analysis will be applied for all analyses. Non-adherent participants to study medication defined as less than 80% of pills being taken will be excluded (see ‘Trial design’) [42, 43].

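### Clozapine use and site stratify the randomisation but are absent from the primary model and the ANCOVA; if they are prognostic, a little precision is forgone

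*Protocol article*

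**What the plan says.** Under Randomization and blinding, "participants will be randomized using block-randomization with a 1:1 allocation to 1) placebo; or 2) metformin", and "Randomization will be stratified for clozapine use versus other antipsychotic use additional to stratification for participating sites". Study setting names three participating sites: "University Medical Centre Utrecht (UMCU), Mondriaan Mental Health Maastricht and GGNet Mental Health in the Netherlands". Two clozapine levels by three sites make six strata.

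Data analysis writes out both models. The primary analysis is a mixed model whose fixed part is listed as "treatment group, baseline weight, gender, age, timepoint (as categorical factor) and compliance with lifestyle therapy as fixed factors"; the only random effect is for the patient. The sensitivity analysis is an "ANCOVA with treatment group and gender as factors and baseline weight and age as covariates". Neither contains clozapine use or site, and site is not a random effect either. The secondary outcomes are to be analysed in a similar way, so the omission carries over to them. Clozapine use returns only as an exploratory subgroup factor. Site appears in no analysis.

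Sample size calculation sizes the trial on an unadjusted two-sample t-test at 26 weeks and adds that linear models will raise efficiency and power.

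**The concern.** Stratified blocks make the arms alike on the stratification factors, which removes between-stratum variation from the true variance of the arm difference. A model without those factors does not know this. It leaves the variation in the residual and reports a standard error that is too large whenever the factors are prognostic. Confidence intervals are then somewhat wide, the test runs somewhat below its nominal level, and some power is forgone.

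This is more than a detail that an article leaves to the analysis plan. The covariate lists are given in full, down to timepoint being categorical, and an analysis plan that followed them would repeat the omission. At stake is part of the efficiency gain that the sample size section expects from the linear model.

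**Working it through.** **Inputs from the article.** Difference 2 kg, SD 4, 128 analysed, two-sided 0.05, power 80%, drop-out at most 50%, about 256 randomised, three sites, two clozapine levels.

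**Assumption.** R² is the share of variance left after baseline weight, age and gender that clozapine use and site explain together. The article gives no figure. I use 0, 0.05 and 0.10.

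**Step 1: the plan's own figure.** The exact two-sample t-test with 64 per arm and effect size 2/4 = 0.5 gives 80.1% power, and 128/(1 − 0.5) = 256. Both stated numbers reproduce.

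**Step 2: standard error without the factors.** The model reports about 4 × √(4/128) = 0.707 kg whatever R² is.

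**Step 3: true standard error.** Blocking balances those randomised, not those who attend week 26. If a fraction f of those randomised is analysed at random, a share (1 − f) of the chance imbalance between strata returns:

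true variance = model variance × [(1 − R²) + R²(1 − f)]

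With f = 0.5 this is model variance × (1 − R²/2).

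- R² = 0.05: ratio of model to true SE = 1/√0.975 = 1.013, so 1.3% too large.
- R² = 0.10: 1/√0.95 = 1.026, so 2.6% too large.

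**Step 4: type I error.** 2 × [1 − Φ(1.96 × ratio)] gives 4.7% and 4.4%.

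**Step 5: power.**

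- Without the factors, Φ[(2 − 1.96 × 0.707)/true SE], with true SE 0.698 and 0.689, gives 81.0% and 81.4%.
- With the factors, Φ[2/(0.707 × √(1 − R²)) − 1.96] gives 82.7% and 84.6%.
- The gaps of 1.6 and 3.3 points are a ceiling, because the adjusted formula ignores the small cost of imbalance among completers and of the extra degrees of freedom.

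**Step 6: simulation of the week-26 comparison with drop-out.** 256 were randomised in six strata and 128 analysed at random, with 12,000 trials per setting. Blocks of 4 and 40% on clozapine are assumptions.

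| R² | SE too large by | Type I error | Power without / with factors |
|---|---|---|---|
| 0.05 | 1.3% | 4.8% | 81.1% / 81.9% |
| 0.10 | 2.5% | 4.3% | 80.1% / 82.7% |

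The Monte Carlo error of a 5% rate over 12,000 trials is √(0.05 × 0.95/12,000) = 0.2 points. The type I error at R² = 0.05 therefore cannot be told apart from 5%.

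**Step 7: the ends of the range.** With no drop-out, simulation with 128 randomised and all analysed puts the SE about 2% (R² = 0.05) and 4% (R² = 0.10) too large. Since 50% is the stated maximum, lower drop-out moves the result towards these values. At R² = 0, adding the factors (1 degree of freedom for clozapine, 2 for site) leaves exact-t power at 80.1%.

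**The case against.** The strongest reply is that no inference is endangered. The trial was sized on an unadjusted test ("A regression of weight on treatment with a sample size of 128 observations achieves 80% power at a two-sided 0.05 significance level"), and every unadjusted power figure above is at or above 80%. The direction is conservative. This stands: what is lost is extra precision, not validity.

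Four stronger readings are tempting, and the article does not support them.

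- **That the standard errors are overstated as a matter of fact.** This holds only if the factors explain variance beyond the covariates already in the models, and no figure is given.
- **That the authors expect clozapine use to be prognostic.** Study population speaks of metformin possibly working differently in the two groups. That is effect modification. It is taken up in the exploratory subgroup analysis, and a main-effect term would not estimate it.
- **That site must matter because the lifestyle programme is delivered locally.** Trial design and COVID-19 measures put the weekly sessions online and describe one programme for all sites. Lifestyle compliance, which is in the primary model, may absorb some of any site difference.
- **That the full textbook overstatement applies.** At R² of 0.05 to 0.10, 1/√(1 − R²) gives 2.6 to 5.4%, but it assumes that the analysed patients are balanced within strata. With the planned 50% drop-out the figure is about half of that.

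What remains is that the listed models do not match the randomisation, and nothing in the article gives a reason for this.

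**Conclusion.** The point holds as a modest and conditional loss of efficiency. The listed models ignore both stratification factors. At an assumed R² of 0.05 to 0.10 with 50% random drop-out, the standard error is about 1 to 2.5% too large, type I error is slightly below 5%, and about 1 to 2.5 points of power are forgone by simulation. At R² = 0 there is no loss.

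The omission by itself does not bias the estimate or inflate type I error, and the 128/256 sample size and its 80% power stand.

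The figures rest on the assumed R², on drop-out unrelated to stratum or outcome, and on a week-26 comparison in place of the full mixed model, which also uses week-13 weights.

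**What to change.** Add two fixed effects, the clozapine stratum and the participating site, to the primary mixed model, the sensitivity ANCOVA and the corresponding secondary-outcome models. Define the clozapine term by the stratum recorded at randomisation and not by current use, because Data analysis expects participants to switch antipsychotic. Make the change before unblinding, so that it cannot look driven by the data.

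The cost is two terms of wording and 3 degrees of freedom. Both variables are already held in the randomisation system, and the sample size does not change.

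### Excluding participants from analysis once their allocation is unblinded contradicts the intention-to-treat principle set for the primary and secondary analyses, and can bias the comparison

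*Protocol article*

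**What the plan says.** The protocol article allocates patients 1:1 to metformin or placebo ("participants will be randomized using block-randomization with a 1:1 allocation to 1) placebo; or 2) metformin"). In the same section, Randomization and blinding, it describes emergency code breaking: "Unblinding for all participating sites will be performed by the study sponsor whenever needed for safety reasons". It then gives the consequence for analysis: "Participants will be excluded from subsequent statistical analyses after unblinding of the treatment allocation". That sentence is not limited to a particular analysis set, endpoint or time window.

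The Data analysis section sets a different rule: "the Intention-To-Treat principle will be followed for the primary and secondary analyses". It does provide a place for exclusions: "In a sensitivity analysis, per-protocol analysis will be applied for all analyses". The criterion given for that set is pill count: "Non-adherent participants to study medication defined as less than 80% of pills being taken will be excluded". Unblinding is not mentioned there.

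The Sample size calculation section defines a drop-out as someone who does not attend at week 26, and closes inclusion when 128 participants have made that visit. Neither rule mentions participants whose code has been broken.

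**The concern.** Intention-to-treat keeps each randomised participant in the assigned arm whatever happens afterwards. A code break happens after randomisation. A rule that removes people because of it cannot stand beside an intention-to-treat primary analysis, and two analysts who each followed one of the two sections would analyse different sets of participants.

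The selection need not be neutral. The stated trigger is safety, and only one arm takes the active drug, so code breaks may be more frequent in one arm or may follow different events in each. Removing those participants makes the arms differ by something other than randomisation.

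The rule also sits badly with the pragmatic design. Under Trial design, participants may continue after giving up the lifestyle intervention or after changing or stopping their antipsychotic, yet a code break would take them out of the analysis.

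**Working it through.** **Inputs.** From Sample size calculation: "a sample size of 128 observations achieves 80% power at a two-sided 0.05 significance level"; the target difference is 2 kg with an SD of 4, and drop-out is at most 50%. From Randomization and blinding: 1:1 allocation. The article gives no unblinding rate, so every share *u* below is an assumption.

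**1. The plan's own figure.** Normal approximation: n per arm = 2 × (1.96 + 0.8416)² × 4² / 2² = 62.8, so 63 per arm or 126 in total. The exact two-sample t-test gives 64 per arm, 128 in total, with 80.1% power. Recruitment: 128 / (1 − 0.5) = 256. The stated figures reproduce.

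**2. What the exclusion sentence removes under each reading.** The mixed model uses the weights at weeks 13 and 26 as outcomes.

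| Time of code break | Participant removed entirely | Only later data removed |
|---|---|---|
| Before week 13 | both weights lost | both weights lost |
| Between weeks 13 and 26 | both weights lost | week 13 kept, week 26 lost |
| After week 26 | both weights lost | both kept, week 52 lost |

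Under the narrower reading, a break before week 26 still discards the primary week-26 weight by rule. The model relies on data being missing at random, and its listed terms (treatment, baseline weight, gender, age, timepoint, lifestyle compliance) do not include the safety event that led to the discard.

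**3. Illustration of bias.** Assume that only metformin participants are unblinded, that they would all have given a week-26 weight, that they have no benefit, and that the other metformin participants have 2 kg. Then the intention-to-treat effect is (1 − u) × 2 + u × 0, and the effect after exclusion is 2.00 kg. The planned standard error is 4 × √(2/64) = 0.71 kg.

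| u | Intention-to-treat | After exclusion | Difference | In standard errors |
|---|---|---|---|---|
| 3% | 1.94 kg | 2.00 kg | 0.06 kg (3%) | 0.08 |
| 5% | 1.90 kg | 2.00 kg | 0.10 kg (5%) | 0.14 |
| 10% | 1.80 kg | 2.00 kg | 0.20 kg (11%) | 0.28 |

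The sign follows from the assumption. If the unblinded metformin participants instead had a 4 kg benefit, the intention-to-treat effect would be 2(1 − u) + 4u = 2.06, 2.10 or 2.20 kg, and exclusion (2.00 kg) would understate it by the same amounts.

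**4. Under no treatment effect.** Suppose the excluded metformin participants did 4 kg worse than their arm's average. The bias is 4u / (1 − u), and the standard error is 4 × √(1/64 + 1/(64(1 − u))). For u = 2%, 5% and 10% the bias is 0.08, 0.21 and 0.44 kg, and the two-sided type I error is about 0.0515, 0.0599 and 0.0939.

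**5. Completers counted but not analysed.** If 2%, 5% or 10% of the 64 completers in each arm were excluded, 63, 61 or 58 per arm would remain (126, 122 or 116 in total). Power would fall from 80.1% to 79.5%, 78.2% or 76.1%.

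**The case against.** The best defence is that *subsequent* limits the rule to data collected after the code break. A break after the week-26 visit would then cost only the week-52 value, and a break between weeks 13 and 26 would leave the week-13 weight in the model. This stands as far as it goes: the primary weight is not always lost. A break before week 26 does lose it, however, and that still conflicts with intention-to-treat.

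Second, the effect may be slight. Code breaks may be rare, some of those unblinded may not attend week 26 in any case (the plan allows for up to 50% who do not), and the illustrated shifts are at most 0.28 standard errors. This also stands, and it limits the expected damage without removing the contradiction.

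Third, a reader might infer that the rule overstates metformin's efficacy by dropping people who did badly on the drug and stopped it. The documents do not support this. They do not say that code breaks fall mainly in the metformin arm, that treatment stops after one, or that a safety event goes with a poor weight result.

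Fourth, a reader might infer that the most serious safety cases vanish. That is also unsupported: the Monitoring section requires the investigator to report every serious adverse event to the sponsor, and the exclusion concerns statistical analyses only.

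**Conclusion.** The contradiction holds at any unblinding rate, and nothing in the article resolves it. It is not a detail left to an analysis plan that is not shown, because the article itself states both rules. Since the exclusion depends on a post-randomisation safety event that may differ by arm, bias in the treatment comparison is possible.

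The direction and size of that bias cannot be derived from the documents. The differences of 0.06 to 0.20 kg rest on assumed rates, unblinding in one arm only, no benefit in those unblinded, and full week-26 attendance among them. The type I error figures rest on an assumed 4 kg deficit. If unblinding were unrelated to both arm and outcome, the cost would be lost precision only. The case for changing the text rests on the conflict over who belongs in the primary analysis, together with the mismatch between completers counted and completers analysed, and not on a demonstrated distortion.

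**What to change.** In Randomization and blinding, delete the exclusion sentence, or restrict it to a labelled sensitivity or per-protocol analysis and list unblinding among that set's criteria under Data analysis. State that all randomised participants, including those unblinded, are analysed in their randomised arm with all available weights. Report code breaks by arm, with timing and reason. A safety code break made through the protocol's own procedure follows the protocol, so it need not be classed as a deviation.

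The cost is about one sentence of text and a short table in the report. The targets of 128 completers and 256 recruited stay as they are, and the rule for stopping inclusion then counts the same people that the primary analysis uses. The change should be made before the database is locked, so that the analysis set is not argued over with results in view.
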